### Data collection

#### Descriptive measures

Demographical information, including age, gender, length of time in nursing home, Mini Mental State Examination (MMSE) score, co-morbidities, medications, use of walking aid and current PA habits, will be collected to describe both groups at baseline.

#### Feasibility data

The feasibility of the study processes are key outcomes of this study. During the recruitment process, the proportion of nursing homes which satisfy the inclusion criteria, reasons for ineligibility of remaining nursing homes and the proportion of invited nursing homes that agree to participate will be recorded. Similarly, for participant recruitment, the proportion of residents in each care home who are eligible and who accept to participate will be documented, as well as reasons for ineligibility and lack of interest. This will elucidate if the eligibility criteria for nursing homes and participants are appropriate or too restrictive. The time taken for recruitment of nursing homes and participants will be documented. Attrition rates of the nursing homes and participants at each time point will be documented. The length of time and number of visits required to collect each outcome from participants will be documented, as well as the proportion of missing data. The components of the study which are critical to enabling a future definitive RCT will be assessed using the progression criteria outlined in Table 5. The cut-off values for each criterion are based on average rates reported by studies in a previous systematic review [7]. A traffic light system of green (continue without modifications – feasible as is), amber (continue, but modify protocol – feasible with modifications) and red (stop – main study not feasible) will be used, as advised by the Medical Research Council Hubs for Trials Methodology Research [32].

**Table 5 Tab5:** Criteria for progression of pilot feasibility study to a definitive trial

Feasibility outcome	Progression criterion
Recruitment	
1. Proportion of eligible nursing homes which agree to participate in study	≥ 70% of eligible nursing homes agree to take part in the study, proceed; 30–70% agree to take part, modify protocol; < 30% agree to participate, do not proceed.
2. Adequate participant recruitment rate	Recruitment rate in each nursing homes of > 80% of required (*n* = 16), proceed; 60–80% of required (*n* = 12–15), modify protocol; < 60% of required (*n* < 12), do not proceed.
3. Average time for recruitment of nursing homes and participants	Nursing homes Measured from initial contact to decision to participate: If < 4 weeks, proceed; if 4–8 weeks, modify protocol; if > 8 weeks, do not proceed Participants Measured from initial contact to consent obtained: If < 3 weeks, proceed; if 3–5 weeks, modify protocol; if > 5 weeks, do not proceed
Outcome assessment	
4. Adequate retention rate of nursing homes and participants at 3-month and 12-month follow-up	Nursing homes Both nursing homes are required to complete the 12-month follow-up; Participants Measured using the following scale in both the intervention and control group: At 3 months: if > 80% retained, proceed; if 60%–80% retained, modify protocol; if < 60% retained, do not proceed At 12 months: if > 70% retained, proceed; if 40%–70% retained, modify protocol; if < 40% retained, do not proceed
Protocol adherence	
5. Adequate adherence rates of participants to the intervention	> 80% of the participants in the intervention arm complete 75% of their physical activity programme, proceed; 60–80% of participants complete 75% of the physical activity programme, modify protocol; < 60% of participants complete 75% of physical activity programme.

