### Sample size calculation

An objective of this study is to assess the feasibility of recruiting and retaining the required number of participants per nursing home which would be needed in a definitive RCT. Therefore, the sample size calculation for this pilot feasibility study is based on the estimated power calculation for a definitive cluster RCT using the primary outcome measure, the Timed Up and Go (TUG) test [23]. In the absence of normative TUG data for an Irish cohort of older adults living in nursing homes, sample size calculations for a definitive RCT were estimated using a New Zealand sample of older adults living in residential care [12]. The sample size requirements for a definitive RCT were calculated as being a minimum of four clusters of size 20 in each arm, in order to have 80% power (α = 0.05) to detect a mean change in TUG score of 4.7 s (± 6.8 s). The current study will recruit one nursing home for each arm. The desired number of participants in each nursing home will be maintained as 20 in order to assess the recruitment potential, recruitment time and feasibility of delivering the intervention to this number of participants. The number of participants lost to follow-up per nursing home will be recorded to inform the final numbers needed when recruiting to the definitive RCT.

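### Table 5 gives two different verdicts at two green/amber cut-offs: 16 recruits in a home, and exactly 70% of eligible homes

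*Protocol article*

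**What the plan says.** The Sample size calculation section fixes the denominator: "The desired number of participants in each nursing home will be maintained as 20".

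Table 5, in the Feasibility data section, then sets the traffic-light bands. Criterion 2 (participant recruitment, applied in each home) reads:

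- green, then amber: more than "80% of required (*n* = 16), proceed; 60–80% of required (*n* = 12–15), modify protocol"
- red: "< 60% of required (*n* < 12), do not proceed"

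Criterion 1 (agreement of nursing homes) sets green and amber as "≥ 70% of eligible nursing homes agree to take part in the study, proceed; 30–70% agree to take part, modify protocol", with red below 30%.

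The text before the table defines the colours for all criteria: green is to continue as is, amber is to continue with a modified protocol, and red is to stop because the main study is not feasible.

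**The concern.** A progression rule should give one verdict for each possible result. In criterion 2 the percentages exclude 80% from green, while the bracketed counts include 16, which is 80% of 20. In criterion 1 the green band includes 70% and the amber band also runs up to 70%.

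The article uses Table 5 to judge the components critical to a definitive trial, and its Discussion counts the progression criteria among the study's strengths. If a result falls on one of these two points, the choice between leaving the protocol alone and modifying it is not fixed in advance. It could be made after the result is seen.

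**Working it through.** **Inputs.** Required number per home: 20 (Sample size calculation). Bands: Table 5, criteria 1 and 2. The number of eligible homes and the expected recruitment rate are not given.

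**Criterion 2.** Divide each count n by 20, then classify it once by the printed percentages (green above 80%, amber 60–80%, red below 60%) and once by the printed counts (green from 16, amber 12–15, red below 12).

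| n | n/20 | By percentage | By count |
|---|---|---|---|
| 10–11 | 50–55% | red | red |
| 12–15 | 60–75% | amber | amber |
| 16 | 80% | amber | green |
| 17–20 | 85–100% | green | green |

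The printed counts therefore cannot be reproduced from the printed percentages. Strictly more than 80% of 20 needs n > 0.80 × 20 = 16, so at least 17 (85%). The band 60–80% of 20 runs from 0.60 × 20 = 12 to 0.80 × 20 = 16, not 15. The red cut-off does agree: below 60% is n < 12 either way. Each set of bands is free of overlap on its own; the conflict lies between the two sets, and only at 16.

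**Criterion 1.** Exactly 70% of N eligible homes means k = 7N/10 homes agreeing. Because 7 and 10 share no factor, k is a whole number only if N is a multiple of 10. Taking N up to 40 as an assumed range, the cases are 7/10, 14/20, 21/30 and 28/40. For any other N the overlap has no effect.

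**Other rows.** Participant retention at 3 months (above 80%, 60–80%, below 60%) and at 12 months (above 70%, 40–70%, below 40%) has bands that do not overlap and carries no counts. The same holds for adherence (above 80%, 60–80%, below 60%).

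**How often would 16 occur?** The documents do not allow an answer. As an illustration only, treat the count as Binomial(20, p), so that P(16) = 4845 × p^16 × (1 − p)^4. This gives 0.035 at p = 0.6, 0.218 at p = 0.8 and 0.090 at p = 0.9. At p = 0.8, P(green) for one home is 0.630 if green starts at 16 and 0.411 if it starts at 17. The model is crude. Twenty is a recruitment target in homes with a capacity of at least 45, not a series of 20 approaches each with the same chance of success.

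**The case against.** The strongest reply is that these are drafting slips with an obvious reading. In criterion 2, green is tagged 16 and amber is capped at 15, which suggests that a strict inequality was printed where at least 80% was meant. In criterion 1, the explicit inequality in the green band can be taken to govern over a loosely written range. Both readings are reasonable, and they limit the seriousness of the point. They do not remove it. The table itself mixes the two conventions (at least in criterion 1, more than in criteria 2, 4 and 5), so no single rule taken from the table settles 16 of 20.

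A reader might also infer more than the documents support:

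- *That the decision to stop is affected.* It is not. Both conflicts are green against amber, and under both colours the work continues.
- *That the adherence criterion has no consequence in its lowest band.* The row does end, after its less-than sign, at "60% of participants complete 75% of physical activity programme" with no action. But the text before the table defines red as stop, and this is plainly the red band. It is an omission in one cell, not a contradiction.
- *That a result of 16 is likely.* The 0.218 comes from a model whose mean (20 × 0.8 = 16) sits on the disputed count. Nothing in the article supports that rate.
- *That all rows should move to an at-least convention.* Retention and adherence contain no error, and the change would move exactly 80% (or 70% at 12 months) from amber to green, loosening those rules without cause.

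**Conclusion.** The point holds in a limited form. Table 5 contradicts itself at two green/amber cut-offs. For participant recruitment, 16 in a home is green by count and amber by percentage, and it is the only count at which the two differ. For home agreement, exactly 70% is both green and amber, which matters only if the number of eligible homes is a multiple of 10. The first is the more consequential, because 16 of 20 is a possible result in either home.

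This follows from the printed thresholds and the target of 20 per home; no modelling assumption is needed. The practical size is one resident per home and one point on the home-agreement scale. The contradictions are worth correcting because they sit in a stated decision rule and cost almost nothing to remove.

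**What to change.** 1. Make the percentages and counts of criterion 2 agree. Either version is coherent:
   - keep the printed counts: green at 80% or more (n ≥ 16), amber from 60% to below 80% (n = 12–15), red below 60% (n < 12); or
   - keep the printed percentages: green above 80% (n ≥ 17), amber 60–80% (n = 12–16), red below 60% (n < 12).
2. Change the amber band of criterion 1 to 30% to below 70%, leaving green at 70% or more.
3. Date the correction and state whether recruitment counts were already known. Trial status gives recruitment as March to June 2018, and the article was published on 29 August 2018. On that schedule the results for criteria 1 and 2 may have been available by publication, so the change should not be presented as made blind to them unless that was so.
4. Leave the retention and adherence cut-offs as they are. Writing the stop action into the lowest adherence band is optional and purely editorial.

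The cost is a short table correction with a dated note. Nothing changes in recruitment, assessment or delivery of the intervention.

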#### Outcome measurements

Quantitative outcome data will be collected in an unblinded manner from participants at T1 (baseline, pre-intervention), T2 (directly after completion of the intervention at three months) to examine the immediate intervention outcomes and T3 (12 months following the start of the intervention) to examine if the outcomes are sustained beyond intervention completion.

##### Primary outcome measure

The primary outcome measure will be physical mobility using the Timed Up and Go (TUG) test [23]. This measures the time taken by an individual to stand up from a standard arm chair, walk a distance of 3 m at a comfortable pace, turn, walk back to the chair and sit down. This test has been shown to predict morbidity and mortality in different populations [33, 34] and is recommended by the American Geriatrics Society and British Geriatrics Society as an indicator of function, mobility and falls risk. The time to complete the task is measured in seconds with a stopwatch. Timing commences on the command ‘go’ and stops when the participant is back sitting down. The TUG will be conducted twice and the average of both attempts will be taken. Participants are permitted to use routine walking aids. Inter-rater and intra-rater reliability is very high for this test among community-dwelling older adults [35, 36] and it is sensitive to change [37].

##### Secondary outcome measures

The Nottingham Health Profile [38] will be used to measure health-related quality of life. This questionnaire measures self-perceived health across six domains: (i) sleep; (ii) mobility; (iii) energy; (iv) pain; (v) emotional reactions; and (vi) social isolation. It has been shown to be reliable, valid [39] and acceptable to older adults, including those with cognitive impairment [40]. The ‘yes/no’ response format makes it easier to administer, than multiple choice Likert scales of other questionnaires. This questionnaire will be administered by the researcher as a structured interview with the participant, as completion rates of questionnaires in older adults tend to improve when the questionnaire is interviewer-administered [41].Gait speed will be assessed using the 10-Metre Walk test. Gait speed is an important objective measure of functional mobility, particularly for older adults [42] and is related to various health outcomes, including functional decline and mortality [43]. The participant will walk 10 m and the time is measured for the intermediate 6 m to allow for acceleration and deceleration. The timer is started when the toes of the leading foot cross the 2-m mark and stopped when the toes of the leading foot cross the 8-m mark. This measure has good inter-rater and intra-rater reliability [42, 44].The Investigating Choice Experiments for the Preferences of Older People Capability index (ICECAP-O) [45] assesses quality of life more broadly than health-related quality of life. It will provide a measure of capability across the dimensions of attachment (love and friendship), security (thinking about the future without concern), role (doing things that make you feel valued), enjoyment (enjoyment and pleasure) and control (independence). Each dimension has four response options that are described as statements representing: none; a little; a lot; and full capability. It has shown good validity for use in older adults living in nursing homes [46] and those who have mild to moderate cognitive impairment [46, 47].The degree of goal attainment as per the Bangor Goal Setting Interview will be reassessed at each follow-up assessment in the intervention group only. The participant will be assisted in re-rating their current performance and satisfaction with performance for their activity-based SMART goal. The researcher will also assess the extent of progress toward achieving the goal using the previously specified goal attainment indicators.

#### Adverse events

It is not anticipated that participants will be at any risk of harm. While falls are a frequent occurrence in nursing homes, safeguards will be in place to reduce the risk of falls and other adverse events (AE), for example, the prerequisite of GP clearance to participate and an individualised activity programme based on physiotherapy assessment. AEs which do occur will be documented by staff on an Adverse Event Reporting Form. The staff will follow the existing policy within the care home relating to the management of a fall or other AE. The researcher will examine AEs on each support visit and make alterations to the PA programme where appropriate.

### Health economic analysis

A preliminary health economic assessment of the intervention relative to the usual care control will be conducted using a cost-effectiveness analysis and cost-utility analysis. The evaluation will be undertaken in a manner consistent with the guidelines issued by Health Information and Quality Authority for the assessment of healthcare interventions and technologies in Ireland. Resource use associated with delivery of the PA intervention will be measured and costed. In particular, resources relating to educational sessions, healthcare professional time input, consumables and materials, equipment and overheads will be measured. A form detailing the resources used by participants over the previous three months, including health service usage, medication usage and private healthcare or study expenses will be completed in both intervention and control groups at baseline, three-month and 12-month follow-up. The researcher will gather this information in consultation with the lead nurse involved in the study, the participant and the participant’s medical notes. The time taken and sources used to obtain this information will be recorded by the researcher. Unit costs will be applied to convert data on resource use to resource costs and total cost variables will be calculated. Data collected from the primary outcome measure, the TUG, at each time point will be used alongside resource usage to provide the basis for the cost-effectiveness analysis. For the cost-utility analysis, effectiveness will be evaluated based on the quality-adjusted life year, which is the preferred outcome measure for economic evaluation and which will be estimated using the EuroQol EQ-5D-5 L instrument [48], assessed baseline, three-month and 12-month follow-up. An incremental cost-effectiveness analysis will be undertaken to provide information on the marginal costs and marginal effects of the intervention relative to the control. The output from the pilot study will provide information on the potential costs and cost-effectiveness of the intervention, as well as the feasibility of collecting the required data, which will inform the design of a definitive RCT.

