**Secondary research questions**	
What are the preliminary clinical outcomes and cost-effectiveness of the intervention compared to the control group? • What are the estimated outcomes of the intervention in comparison with the control group and are these sustained at 12-month follow-up? • What are the costs of the intervention in comparison to costs in the control group?	

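### Care resource use in months 3 to 9 is not collected, so a 12-month cost or cost per QALY would rest on an assumption for half the follow-up

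*Protocol article*

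**What the plan says.** The Protocol article, under Health economic analysis, specifies one form: "A form detailing the resources used by participants over the previous three months, including health service usage". It "will be completed in both intervention and control groups at baseline, three-month and 12-month follow-up". On sources it says: "The researcher will gather this information in consultation with the lead nurse involved in the study, the participant and the participant’s medical notes". Delivery of the programme is measured and costed separately.

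The effect side of the cost-utility analysis is the QALY, "which will be estimated using the EuroQol EQ-5D-5 L instrument [48], assessed baseline, three-month and 12-month follow-up". TUG at each time point serves the cost-effectiveness analysis. Costs are to be totalled, and marginal costs set against marginal effects.

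The time points are defined under Outcome measurements: "T2 (directly after completion of the intervention at three months", and "T3 (12 months following the start of the intervention) to examine if the outcomes are sustained beyond intervention completion". Table 1 lists as a secondary question "What are the costs of the intervention in comparison to costs in the control group". It places the feasibility of collecting economic data, meaning which sources serve and how long it takes, under a primary question.

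**The concern.** The look-back length and the completion times are both stated, and together they leave a hole. Three months of recall at month 12 reaches back only to month 9, whereas the preceding form stopped at month 3. The missing stretch starts as the supported programme ends, which is when care use in the two homes could begin to differ or to converge.

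The comparison of yearly costs is at stake, and with it any yearly cost per QALY. The pilot is also meant to show how feasible economic data collection is. Run as described, it would record the sources and effort needed for three-month windows but not what it takes to assemble a full year of costs, which a later trial with 12-month follow-up would want to know.

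**Working it through.** The plan states no figure to reproduce for this point. The check is interval arithmetic on the stated schedule.

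**Inputs** (Protocol article, Health economic analysis and Outcome measurements)
- Look-back of the form: L = 3 months.
- Completion times: t = 0, 3 and 12 months, with baseline taken as the start of the intervention.
- EQ-5D-5L times: 0, 3 and 12 months.
- Programme length: 3 months.

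**Cost coverage.** A form at month t covers [t − L, t].
- t = 0: [−3, 0], before the intervention.
- t = 3: [0, 3].
- t = 12: [9, 12].
- Covered after baseline: 3 + 3 = 6 months.
- Uncovered: [3, 9], which is 6 months.
- Share of follow-up uncovered: 6/12 = 50%.
- Share of the post-intervention period uncovered: 6/9 = 67%.

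**QALY coverage.** The article names no rule. Assuming the usual trapezoid rule, with utilities u0, u3 and u12:

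QALY = (3/12)(u0 + u3)/2 + (9/12)(u3 + u12)/2 = 0.125 u0 + 0.500 u3 + 0.375 u12.

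The weights sum to 1.0 year. Months 3 to 12 make up 9/12 = 75% of that year, and care costs are observed for only 3/9 = 33% of that segment.

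**Effect on the incremental cost.** Let P be the programme delivery cost, and let d1, d2 and d3 be the monthly between-arm differences in care cost over months 0–3, 3–9 and 9–12.
- True 12-month increment: P + 3·d1 + 6·d2 + 3·d3.
- Sum of the two observed windows: P + 3·d1 + 3·d3.
- Omitted: 6·d2.

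With a steady difference (d1 = d2 = d3 = d), the true increment is P + 12d and the simple sum is P + 6d. The care-cost part is halved and P is untouched, so the error does not cancel between arms.

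**If the gap is filled.** Setting d2 = (d1 + d3)/2 gives a care-cost increment of 3·d1 + 3·(d1 + d3) + 3·d3 = 6·(d1 + d3), which is twice the observed sum. That is exact when the difference is steady. Otherwise the error is 6 × (d2 − (d1 + d3)/2), and no planned form yields d2.

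**After the change.** A nine-month look-back at month 12 covers [3, 12], so the uncovered time falls from 6 months to 0.

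**The case against.** The gap itself is hard to dispute, but several readings built on it go too far.

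- **Costs over 6 months will be divided by QALYs over 12.** A reader might infer this. The article states no time horizon, no QALY rule and no rule for building total costs, and an article may leave these to a fuller document. The 12-month horizon is implied by the EQ-5D-5L times, not stated. What stands is that any 12-month total needs an assumption for months 3 to 9, because the form does not observe them.
- **Costs will be halved.** This holds only if the two windows are added with no extrapolation. Under the same premise of constant cost, simple scaling recovers the total. The halving never applies to programme delivery.
- **Cost per second of TUG is wrong.** TUG is a point measure, and the 0 to 3 month window has complete costs. Only a version using 12-month cumulative costs is touched.
- **The schedule could not support the definitive trial.** The pilot is meant to inform that trial's design, so its schedule is not fixed in advance.

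The short window may also be deliberate. Participants are one of the sources and include people with dementia (Discussion), and some items, such as private expenses, may not be in the notes. This argues against a uniform nine-month recall but not against a longer review of records.

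Finally, the economic comparison is secondary, is called preliminary, uses one home per arm, and enters no progression criterion in Table 5. This lowers the severity and leaves the gap in place.

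**Conclusion.** The point holds in a limited form. As scheduled, care resource use is uncollected for 6 of the 12 follow-up months, and nothing else described in the article fills that period: there is no interim form, and the separately costed programme ends at month 3. A 12-month incremental cost, and so a 12-month cost per QALY, would depend on an unobserved assumption for half the follow-up. The size of any resulting error is unknown. It is half of the care-cost difference if that difference is steady and the windows are merely summed, and nil if it is steady and the gap is scaled up. It can go either way if months 3 to 9 differ from the neighbouring windows. This rests on the form being used as described and on a 12-month horizon being intended.

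The 0 to 3 month analyses stand. Severity is moderate. No progression decision depends on this, but the feasibility of collecting economic data belongs to a primary research question.

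**What to change.** At T3, extend the look-back to the nine months since T2 for items obtainable from the medical and medication records and from the lead nurse, all within the sources the plan already uses. Keep the three-month window for items that depend on the participant's recall, such as private expenses. Record the extraction time for the longer window, since that is itself a feasibility result.

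If this is not done, take one of two courses and state it in the analysis plan:
- Limit the cost-effectiveness and cost-utility analyses to 0 to 3 months.
- Present the 12-month result only with an explicit assumption for months 3 to 9 and a sensitivity analysis around it.

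The cost is some extra record extraction for at most 40 residents (20 per home), and weaker data for items not held in records. Only the T3 form changes. With recruitment from March to June 2018 (Trial status), T3 falls in 2019, so the baseline and three-month forms are unaffected.
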